### Sample size

Based on the study objectives, recruitment feasibility, and the desired precision of estimates (i.e., two-sided 95% confidence intervals [CIs]), the sample size was calculated using PASS Sample Size software. Antibiotic use will be compared between both Arm 2 and Arm 3 versus Arm 1 (*N* = 1500) at the first consultation and will serve as a secondary outcome. The effect of the educational measures on the use of OTC antibiotics will be compared between Arm 2 and Arm 3 (*n* = 1000) at 4 weeks and 4 months of follow-up.

It is estimated that approximately 85% of women in LLMICs are over-treated with antibiotics for VD, and around 50% receive antibiotics that contribute to AMR. Furthermore, about 40% of women are expected to purchase antibiotics OTC. The overtreatment with antibiotics and the use of AMR will be assessed at the first consultation whilst the adherence to the treatment recommendation will be assessed at 4 weeks as primary outcome and at 4 weeks and 4 months of follow-up as secondary outcome.

With 1500 participants randomized equally across the three arms (allocation ratio of 1:1:1), a 10–20 percentage point difference between groups in any of these measures will produce CIs with a width of 8–12%, achieving at least 90% power for each comparison at a significance level of 0.017 (adjusted from 0.05 to account for multiplicity with three primary outcome measures). For the assessment of over-the-counter antibiotic use, even with a 40% loss to follow-up, the expected CI width remains around 15%.

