### Outcomes

The primary outcome measures are:The proportion of participants overtreated with antibiotics at the primary consultation with the health practitioner Overtreatment is defined as receiving a cephalosporin and/or macrolide when *Ng* is negative; a tetracycline or macrolide when *Ct* is negative; or a nitroimidazole when the gold standard test for *Tv* or BV is negative, (medications as specified in the Nepali STI case management guidelines) [15] (comparing arm 1 with the combined arms 2 and 3).The proportion of participants prescribed AMR driving antibiotics (Cephalosporins, Azithromycin, Ciprofloxacin) at the primary consultation with the health practitioner. comparing treatment as usual (arm 1) with POCT-based treatment (arms 2 and 3).The proportion of participants adhering to treatment recommendations, comparing arms 2 and 3. Adherence is assessed during telephone follow-ups after one month and is defined as follows: (a) participants report that they took the prescribed medication; (b) no additional purchase of antibiotics; and (c) no purchase of other medication for VD.

The study also examines six secondary outcome measures at various time points. The baseline data from this trial will also contribute to the analysis of the epidemiology of VD and infection including psychosocial factors, and measure the diagnostic accuracy of the POCT.

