#### Primary outcome analyses

Two of the three primary endpoints (a) the proportion of participants overtreated with antibiotics and (b) the proportion of participants being prescribed AMR-driving antibiotics will be compared between groups (Arm 1 *vs* Arm 2 + 3). The third primary endpoint, (c) the proportion adhering to treatment recommendations at 1 month follow-up, will be compared between groups Arms 2 vs 3. The risk difference and corresponding 95% confidence intervals, as well as p-values calculated from chi-squared tests, will be reported. *P*-values below 0.017 will be regarded as statistically significant due to there being three primary outcomes.

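### The stated power of at least 90% at 0.017 for a 10–20 point difference does not hold at 10 points for Arm 2 versus Arm 3, where it is about 82% with full follow-up

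*Protocol article*

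**What the plan says.** The Sample size section of the protocol article plans 1500 participants in a 1:1:1 ratio, so 500 per arm. It expects rates of about 85% for overtreatment, 50% for antibiotics that drive antimicrobial resistance (AMR) and 40% for OTC antibiotic purchase. It describes the design as "achieving at least 90% power for each comparison at a significance level of 0.017". The level is 0.05 adjusted for three primary outcomes. The effect sizes to which this applies appear in the same sentence, tied to a statement of precision: "a 10–20 percentage point difference between groups in any of these measures will produce CIs with a width of 8–12"%. On attrition it adds, for OTC use, that "even with a 40% loss to follow-up, the expected CI width remains around 15"%.

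The Outcomes section lists the third primary outcome as "The proportion of participants adhering to treatment recommendations, comparing arms 2 and 3", assessed by telephone after one month. The Primary outcome analyses section gives risk differences with 95% intervals, "as well as p-values calculated from chi-squared tests, will be reported", and says that p-values below 0.017 "will be regarded as statistically significant due to there being three primary outcomes".

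Early in the Sample size section, antibiotic use is compared between Arm 1 and Arms 2 and 3 "at the first consultation and will serve as a secondary outcome". The Outcomes and Primary outcome analyses sections make overtreatment and prescription of AMR-driving antibiotics, both recorded at that consultation, primary.

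**The concern.** The power statement covers every comparison and every measure, over a range that starts at 10 points. The first two primary outcomes compare 500 with 1000 participants. The third compares 500 with 500, at a rate where the binomial variance is large, and under the same reduced significance level. One power figure is unlikely to fit all three.

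Adherence is the only primary outcome that tests what the education and psychosocial package adds to test-guided treatment. If the comparison is published as having at least 90% power at 10 points, a non-significant result will be read as stronger evidence against a 10-point benefit than the design can supply.

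**Working it through.** **Inputs.** From the Sample size section: 500 per arm; rates 85%, 50% and 40%; smallest difference 10 points; level 0.017; 40% loss, which leaves 300 per arm. From the Primary outcome analyses section: chi-squared test, Arm 1 versus Arms 2 + 3 (500 versus 1000) for the first two outcomes, and Arm 2 versus Arm 3 (500 versus 500) for the third. The test is taken as two-sided, as the chi-squared test and the two-sided intervals imply.

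**Formulas.**
- SE1 = √[p1(1−p1)/n1 + p2(1−p2)/n2]
- SE0 = √[p̄(1−p̄)(1/n1 + 1/n2)], with p̄ the pooled proportion
- 95% interval width = 2 × 1.96 × SE1
- Power = Φ[(|p1−p2| − z × SE0)/SE1], with z = 2.387 for two-sided 0.017 and 1.960 for two-sided 0.05

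**Step 1: reproduce the protocol's interval widths.**
- 85% v 75%, 500 v 1000: SE1 = 0.02104, width 8.2%
- 50% v 40%, 500 v 1000: SE1 = 0.02720, width 10.7%
- 40% v 30%, 500 v 500: SE1 = 0.0300, width 11.8%
- 40% v 30%, 300 v 300: SE1 = 0.03873, width 15.2%

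The first three match the stated 8–12% and the last matches the stated 15%. These therefore appear to be the inputs that the protocol used.

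**Step 2: power at 10 points with the same inputs, two-sided 0.017.**

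| Comparison | SE0 | (0.10 − 2.387 × SE0)/SE1 | Power |
|---|---|---|---|
| 85% v 75%, 500 v 1000 | 0.02257 | 2.19 | 98.6% |
| 50% v 40%, 500 v 1000 | 0.02714 | 1.29 | 90.2% |
| 40% v 30%, 500 v 500 | 0.03017 | 0.93 | 82.5% |

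The third falls short. At two-sided 0.05 it becomes (0.10 − 1.960 × 0.03017)/0.0300 = 1.36, or 91.3%. With unpooled variance at 0.017 it is 82.8%, so the choice of formula does not matter. A one-sided test at 0.017 would give 88.5%, still below 90%.

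**Step 3: the difference at which the claim becomes true.** From 40% downwards with 500 per arm, 90% is reached at 11.05 points, and at 15 points power is 99.7%.

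**Step 4: dependence on the rate.** The protocol gives no rate for the adherence composite. For a 10-point difference with 500 per arm at 0.017:
- 45% v 55%: 78.2% (the minimum)
- 40% v 50%: 78.7%
- 60% v 70%: 82.5% (mirror image of 40% v 30%)
- 20% v 30%: 89.9%
- 10% v 20%: 98.0%

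Power is below 90% for pairs from about 20% v 30% to about 70% v 80%.

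**Step 5: the 40% loss scenario.** With 300 per arm and 40% v 30%, SE0 = 0.03894 and (0.10 − 2.387 × 0.03894)/0.03873 = 0.18, which gives 57.2%. Power of 90% then needs 14.05 points, and at 15 points power is 94.0%.

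**The case against.** The strongest defence is that the shortfall is narrow. It occupies about the first point of a 10–20 point range, and over most of that range the comparison has well over 90% power. That is correct, and it rules out reading the comparison as underpowered throughout. It does not rescue the sentence, which includes 10 points and says that each comparison qualifies.

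A second defence is that 40% is an OTC purchase rate, whereas adherence has three components and could be much lower, where the variance is smaller and power higher. This also stands in part. A reader might infer that, since 40% buy antibiotics, adherence lies near 60% and power cannot be better than calculated here. The documents do not support that: a low composite rate, such as 10% v 20%, would meet the claim, and a general expectation about purchasing need not equal the rate of additional purchase in Arm 2. The 82% is therefore conditional for adherence. For OTC purchase itself, one of the measures the sentence covers, it follows from the protocol's own rate.

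A reader might also take the 57% as contradicting the protocol. It does not. The 40% loss is a stress case attached to an interval width for OTC use, that width reproduces, and no power is claimed under it. The missing-data section treats missingness above 20% on this outcome as a contingency.

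Nor are the interval widths wrong because they are not at the 0.017 level. They are labelled as 95% intervals, and 95% intervals are what the analysis section will report.

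On the secondary-outcome label, overall antibiotic use could be one of the six secondary outcomes that the article mentions without listing. The wording is then ambiguous rather than plainly wrong, but the paragraph does not separate overall use from the two prescribing outcomes that are primary.

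**Conclusion.** The power statement is wrong as written for Arm 2 versus Arm 3 at the lower end of its own range. With 40% versus 30%, 500 per arm, full follow-up and two-sided 0.017, power is about 82% against a stated minimum of 90%, and 90% is reached from about 11 points. For adherence this rests on borrowing the OTC rate. Over the rates in the working, a 10-point difference has about 78% to 98% power. The two first-consultation outcomes satisfy the claim at 10 points, the AMR outcome only just.

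The 90% is met at 0.05 and missed at 0.017, so a reader might infer that the power was not recalculated after the multiplicity adjustment. That is plausible, but the documents do not say so and the finding does not need it.

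The secondary-outcome wording is a separate labelling inconsistency with no bearing on the arithmetic.

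**What to change.** In the Sample size section:

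- Limit the statement of at least 90% power at 0.017 for a 10-point difference to overtreatment and AMR-driving antibiotics.
- For Arm 2 versus Arm 3 adherence, state about 82% power at 10 points and 90% at about 11 points with full follow-up. Name the assumed 40% rate and say that it is the OTC purchase rate, used because no composite adherence rate is available.
- Beside the existing 40% loss sentence, add the consequence for power: about 57% at 10 points, and 90% at about 14 points.
- Reconcile the phrase that makes first-consultation antibiotic use secondary with the Outcomes and Primary outcome analyses sections, either by correcting it or by saying which measure of use is meant.

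The cost is rewording and a less favourable figure for one comparison. The Trial status section reports recruitment of 1500 complete, so the sample size does not change. The correction should be made before the adherence comparison is analysed, so that the result is read against the right power.

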### Randomization and blinding

After obtaining informed consent, RAs open consecutively numbered, sealed opaque envelopes containing the randomized group assignment. Randomization is computer-generated using a simple randomization method (Research Randomizer©). Participants are blinded to their group assignment. Each PID (1–1500) was assigned to one of the three trial arms (1, 2, 3) based on pseudo-random numbers uniformly distributed between 0 and 1, with equal probability of allocation to each group.

The resulting allocation list was generated by an independent researcher and implemented on site using consecutively numbered, sealed opaque envelopes containing the randomized group assignment. We opted not to stratify or block to keep field procedures straight forward and robust in this multi-site and resource-limited setting. This reduced the risk of errors in envelope handling and simplified implementation for rotating staffs. Due to the nature of the intervention, only RAs performing follow-up and the statistician are blinded to group allocation. HPs are informed about whether they will receive POCT results but blinded as to whether participants receive educational materials or are offered counseling (arm 1 vs. arm 2 and 3).

### Data collection

#### Assessment and data collection procedures

The study’s RAs receive proficiency training before data collection, including a one-day course on Good Clinical Practice. After randomization, participants are provided with verbal and pictorial instructions to guide the self-collection of vaginal swabs and urine samples. Following sample collection, participants complete a study questionnaire using an electronic tablet equipped with a headset, utilizing a Color-coded Audio Computer-Assisted Self Interview (C-ACASI) system [40]. After completing the questionnaire, participants proceed to consultation with a health practitioner.

#### Prescriptions and antibiotic use

The health practitioner completes a questionnaire documenting the antibiotics prescribed—either after the consultation (arm 1) or upon receiving POCT results (arms 2 and 3). If the health practitioner delays prescription while awaiting other tests (e.g., urine), the RA follows up to ensure completion of the questionnaire. These data are entered daily into the case report form (CRF). If insufficient treatment is provided based on gold-standard STI results, this is recorded after the initial prescription is documented, and any additional antibiotics provided are also registered.

#### Laboratory diagnostics

Gold standard STI testing includes the following: *Cepheid GeneXpert*® for *Ct*, *Ng,* and *Tv*. For BV, dried wet mounts from vaginal smears are collected for Nugent scoring and wet mount microscopy. All tests are performed by RAs, except Nugent scoring (performed by microbiologist [name]) and wet mount microscopy (performed by [name]). Nugent scoring is considered the gold standard for BV. For quality control, 10% of slides are double read by a second microbiologist ([name]).

#### Baseline data and secondary outcomes

Baseline data are collected using a C-ACASI with RAs available to assist. This ensures the inclusion of participants with limited literacy. Data are uploaded to a secure cloud and later transferred to the CRF. These data are acquired as follows:

Questions adapted from: WHO clinical study guidance on POCT for VD to establish sociodemographic profile, reproductive and sexual history, and the VD symptoms [41].The Hopkin’s Symptom Checklist for screening anxiety and depression [37, 38].DV screening questions adapted from the 2016 Nepal Demographic Health Survey, which have been validated in Nepali [39].Health practitioners’ documentation of clinical findings on paper questionnaires, which are collected and transferred to the CRF [41].

Secondary outcome data are collected during telephone follow-ups at one- and four-month post-consultation. These follow-ups are conducted using printed questionnaires by RAs who are blinded to group assignments. The information is later entered into the CRF by a researcher.

#### Retention and follow-up

Participants are contacted via telephone up to four times at each follow-up point to maximize retention and reduce loss to follow-up.

#### Process evaluation

A process evaluation is conducted at multiple time points throughout the study’s inclusion period and involves in-depth interviews with participants at DH and the ORCs, focus group discussions with the health practitioners from the obstetrics and gynecology department (pre- and post-trial), stakeholder focus groups, and interviews with the RAs at the end of the RCT.

#### Participant timeline

Figure 2 illustrates the participant timeline.

**Fig. 2 Fig2:**
[figure not shown]
Participant timeline for enrolment, intervention, and assessment. *Gold standard test for bacterial vaginosis is Nugent scoring, which is performed within 6 months on air-dried microscopy slides. **Treatment for missed positive cases (*Ct, Ng, Tv)* is provided after collection of main outcomes (prescription of antibiotics by health practitioners). Abbreviations: AD, anxiety and/or depression; AMR, antimicrobial resistance; Ct, *Chlamydia trachomatis*; DV, domestic violence; HSCL, Hopkins Symptom Checklist; Ng, *Neisseria gonorrhoeae*; OTC, over-the-counter; POCT, point-of-care test; Tv, *Trichomonas vaginalis*; VD , vaginal discharge

### Data management and confidentiality

Data are collected on paper for the molecular tests (*Ct*, *Ng,* and *Tv)*, microbiological tests, Nugent scores, wet mount results, health practitioner documentation, and follow-up interviews. Researchers enter these data into a CRF using an Excel spreadsheet on the project computer. Paper versions are retained for five years. To ensure data quality, principal investigators (PIs) will conduct a random review of 10% of the data entries.

Participant interviews are conducted using C-ACASI on electronic tablets [40]. All user data is password-protected and encrypted before being transmitted to a secure web service. The encrypted data is then downloaded into a CRF on a secure project computer.

At inclusion, each participant is assigned a unique participant identification (PID) number. The connection key, linking the PID to the participant’s name and telephone number, is stored in a locked cupboard, with a backup copy kept on an encrypted USB stick. All data will be anonymized after five years.

### Statistical analysis

Descriptive analysis will be used for demographic characteristics, reproductive history, questions related to VD, clinical findings, working diagnosis by health practitioners, microbiological results, anxiety and depression scores, prevalence of DV, and prescription of medications (including antibiotics). At follow-up, we will describe symptom development, treatment adherence, and patient satisfaction for all participants after one and four months. Anxiety and depression scores will be assessed for the remaining participants at the four-month follow-up, after recruitment is completed, due to time constraints. The expected sample size is approximately 400 participants.

#### Primary outcome analyses

Two of the three primary endpoints (a) the proportion of participants overtreated with antibiotics and (b) the proportion of participants being prescribed AMR-driving antibiotics will be compared between groups (Arm 1 *vs* Arm 2 + 3). The third primary endpoint, (c) the proportion adhering to treatment recommendations at 1 month follow-up, will be compared between groups Arms 2 vs 3. The risk difference and corresponding 95% confidence intervals, as well as p-values calculated from chi-squared tests, will be reported. *P*-values below 0.017 will be regarded as statistically significant due to there being three primary outcomes.

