### Study setting

The study is conducted at Dhulikhel Hospital (DH) and seven of its outreach centers (ORCs) in Bagmati province, Nepal. DH is a non-profit, independent, non-governmental, tertiary hospital located in a semi-urban area of Nepal. It provides healthcare services to approximately 2.7 million people from diverse ethnic backgrounds across the country through 18 ORCs at the grassroots level [35]. The seven ORCs involved in the study were selected based on facility observation checklists (distance from DH, staffing, patient volume, infrastructure) with the aim of being representative of rural Nepal.

At DH, women presenting with concerns about VD are seen by obstetrics and gynecology consultants and resident doctors at the OPD. At the ORCs, these patients are attended by medical officers or obstetrics and gynecology residents.

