#### Protocol adaptation for Tv testing

An unplanned interim analysis was conducted after 218 participants had been enrolled, prompted by concerns that many laboratory-confirmed *Tv* cases had not received treatment due to negative POCT results. Without unblinding or compromising randomization, only the POCT results and gold standard laboratory results for *Tv* were compared. This analysis showed low sensitivity of the pH and whiff test: initial POCT approach (3.7% correctly identified; 7.8% false negatives). For ethical reasons, affected participants were traced and treated, and an additional diagnostic step was added for the remainder of the trial (see “ POCT methods” section).

Although *OSOM®* is a validated diagnostic tool for *Tv* detection, its sequential use following pH and whiff testing has not previously been evaluated [25].

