### Ethical considerations and post-trial care

Prior to the start of participant inclusion, ethical approvals were obtained from the Nepal Health Research Council (NHRC), the Institutional Review Committee of Kathmandu University School of Medical Sciences (IRC-KUSMS), and the Regional Committees for Medical and Health Research Ethics (REK). Any significant amendments to the protocol, such as the addition of an extra test for *Tv* after enrollment of the first half of the participants, are implemented only after obtaining approval from the same ethical committees.

In the case of positive *Ng* results, a new cervical swab will be collected by a health practitioner for culture and AMR testing. Treatment will be adjusted accordingly based on the results.

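### The primary analysis leaves out site and Tv-test period; prespecified adjustment would bring a modest efficiency gain, not a correction of bias

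*Protocol article*

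**What the plan says.** **Allocation** (Randomization and blinding): "Randomization is computer-generated using a simple randomization method", and "We opted not to stratify or block to keep field procedures straight forward and robust". The reason given is operational: simple envelope handling with rotating staff.

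**Sites** (Study setting): one hospital and seven outreach centres. Consultants and residents see patients at the hospital; medical officers or residents do so at the centres.

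**Change during the trial** (Protocol adaptation for Tv testing): "An unplanned interim analysis was conducted after 218 participants had been enrolled", after which "an additional diagnostic step was added for the remainder of the trial". Ethical considerations and post-trial care places the added test "after enrollment of the first half of the participants".

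**Primary analysis** (Primary outcome analyses): "The risk difference and corresponding 95% confidence intervals, as well as p-values calculated from chi-squared tests, will be reported". No covariate is named. Overtreatment and AMR-driving prescribing compare Arm 1 with Arms 2 and 3 combined; adherence compares Arm 2 with Arm 3. Secondary outcome analyses applies the same strategy to the binary secondary outcomes.

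**Site and period** (Subgroup analysis): both classify subgroups for every primary and secondary outcome, with site as hospital versus outreach centres and period as before versus after the added Tv test. Neither enters the primary model.

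**The concern.** Two factors that the protocol considers important enough to split every outcome by are absent from the primary estimate. Nothing in the allocation balances them. If prescribing or adherence varies between sites, that variation stays in the error term of an unadjusted comparison.

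The loss matters most for Arm 2 versus Arm 3, which has the fewest women and depends on telephone follow-up. Recruitment closed at 1500 (Trial status), so precision can no longer be bought with more participants, and covariate adjustment is one of the few means left.

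A period term, like the planned before/after subgroup, also needs one changeover point, and the protocol states none.

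**Working it through.** **Inputs from the protocol.** Sample size: 1500 women at 1:1:1, so 500 vs 1000 (Arm 1 vs 2+3) and 500 vs 500 (Arm 2 vs 3); rates of 85% (overtreatment), 50% (AMR-driving) and 40% (over-the-counter purchase); differences of 10–20 points; alpha 0.017; at least 90% power for each comparison; CI widths of 8–12%, or about 15% after 40% loss. The 40% is the only rate given for Arm 2 vs 3, so it stands in for adherence.

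**Assumptions not in the protocol.** 40% of women at the hospital and the rest spread evenly over seven centres; between-site SD of 0 to 1.0 on the logit scale; period effect of 0 to 0.5 logit; changeover at 218 (218/1500 = 14.5%) or at half (750).

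**1. The plan's own figures.** Power = Φ[(d − z·SE₀)/SE₁], with z = 2.387 (two-sided 0.017), SE₀ pooled and SE₁ unpooled. CI width = 2 × 1.96 × SE₁. At a 10-point difference:

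| Comparison | Rates | n | SE₁ (points) | 95% CI width | Power |
|---|---|---|---|---|---|
| Overtreatment | 85 vs 75% | 500 vs 1000 | 2.10 | 8.2% | 98.6% |
| AMR-driving | 50 vs 40% | 500 vs 1000 | 2.72 | 10.7% | 90.2% |
| Arm 2 vs 3 | 40 vs 30% | 500 vs 500 | 3.00 | 11.8% | 82.5% |
| Arm 2 vs 3, 40% loss | 40 vs 30% | 300 vs 300 | 3.87 | 15.2% | 57.2% |

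The widths reproduce. The 90% claim holds for the first two rows and fails for Arm 2 vs 3 at this end of the range. At 15 points every comparison exceeds 90%.

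**2. Is the crude test valid?** Under simple randomisation the SD of the chance difference in pre-change share, Arm 1 vs 2+3, is √[q(1−q)(1/500 + 1/1000)]: 1.9 points for q = 0.145 and 2.7 points for q = 0.5. If outcomes differ by 10 points between periods, the risk difference moves by 0.10 × 1.9 to 0.10 × 2.7, or 0.2–0.3 points, against a standard error of 2.1–2.7 points. Simulated type I error (nominal 0.017, Monte Carlo SE 0.002) was 0.016–0.021 unadjusted and 0.017–0.022 adjusted. The crude test is sound.

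**3. Variance that adjustment can remove.** The share is Σwₖ(pₖ − p̄)² / [p̄(1 − p̄)].

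- Eight sites, averaged over simulated site effects: 0.6–1.2% at SD 0.25, 2.6–4.5% at SD 0.5, 10–14% at SD 1.0.
- Hospital versus centres only, at a 50% rate: a 10-point gap gives 0.4 × 0.6 × 0.10²/0.25 = 1.0%; a 20-point gap gives 3.8%.
- Period, for a 5–10 point shift: 0.1–0.7% with the cut at 218, 0.3–1.6% with the cut at half.

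Nearly all of the gain comes from site.

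**4. Simulated power at alpha 0.017**, chi-squared test against a risk-difference model with site and period terms and robust SE. Moderate: site SD 0.5, period 0.3 logit, cut at 218. Strong: site SD 1.0, period 0.5 logit, cut at half.

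| Comparison | Scenario | Unadjusted | Adjusted |
|---|---|---|---|
| AMR-driving 50 vs 40% | moderate | 86.4% | 88.0% |
| AMR-driving 50 vs 40% | strong | 76.3% | 83.0% |
| Overtreatment 85 vs 75% | moderate | 95.0% | 96.9% |
| Arm 2 vs 3, 40 vs 30% | no effects | 81.2% | 81.3% |
| Arm 2 vs 3, 40 vs 30% | moderate | 81.9% | 84.3% |
| Arm 2 vs 3, 40 vs 30% | strong | 68.5% | 76.7% |
| Arm 2 vs 3, 40% loss | moderate | 56.4% | 60.0% |

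Site and period effects were added on the logit scale, which alters the marginal rates and differences. Read across each row, not down the columns or against step 1.

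**5. Does adjustment restore 90% for Arm 2 vs 3?** At 40% vs 30% and alpha 0.017, 90% power needs 610 per arm. With 500, adjustment would have to remove about 1 − 500/610 = 18% of the variance. That exceeds the 14% average under the largest assumed site spread, and no simulated scenario reached 90%.

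**The case against.** The strongest reply is that nothing here is an error. With simple allocation the crude risk difference is unbiased, and its interval and test already allow for chance imbalance. No stratification factor is ignored, because there is none. All of this stands. A reader might infer that imbalance in site or period invalidates the primary result; step 2 shows that it does not.

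Second, the protocol nowhere says that prescribing differs by site. Residents work at both the hospital and the centres, and the subgroup section classifies site in two levels, not eight. This also stands: the size of any gain is assumed, and that individual centre is recorded is a reasonable inference rather than a stated fact.

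Third, the added Tv result reaches practitioners only in Arms 2 and 3, so period mainly modifies the Arm 1 vs 2+3 contrast. A main-effect term averages over that change and does not resolve it. The planned before/after subgroup analysis addresses it and must stay.

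Fourth, a reader might infer that the two statements about timing contradict each other. They need not: amendments wait for ethics approval, so a look at 218 women followed by introduction around the halfway point fits both. What remains is that the protocol gives no changeover date.

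Fifth, eight sites by two periods make 16 strata. With a cut near 218 the early period would average 218/(8 × 3), about nine women per arm per site. This limits the form of adjustment, not the principle.

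Last, enrolment is complete, so this changes a stated primary analysis late, and an unseen SAP may already hold a supportive adjusted estimate. The protocol does fix the primary test, however, and a change made before unblinding and documented as such is legitimate.

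**Conclusion.** The point holds as an efficiency recommendation. The planned analysis is valid but leaves out two factors that the protocol itself singles out. Adjustment costs essentially nothing if they prove irrelevant. The gain is nil if sites do not differ, about 2–4% of variance under moderate assumed differences and up to about 14% on average under large ones. Under moderate assumptions that is roughly 2 points of power, or nearly 4 points for Arm 2 vs 3 with 40% loss. These figures rest on an assumed hospital share and assumed site and period effects.

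Two stronger conclusions are not supported. Adjustment does not remove a bias, and it does not repair the power shortfall for Arm 2 vs 3, which is a separate matter and itself rests on using the over-the-counter purchase rate for adherence.

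**What to change.** Before unblinding, and recorded as a dated change:

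- Make the primary estimate for each outcome a risk difference adjusted for site and Tv-test period, with a matching p-value judged against 0.017. One form is logistic regression with main effects, standardised to a marginal risk difference with robust SE. Another is a Mantel-Haenszel risk difference, pooling small outreach centres if strata are sparse. Both keep the result on the risk-difference scale.
- Name the levels of site and any pooling rule in advance, without reference to outcomes by arm.
- Report the crude risk difference and chi-squared test as supportive.
- Keep the before/after Tv-test subgroup analysis for the Arm 1 vs 2+3 contrasts.
- State the date on which the added Tv test came into use and the number enrolled by then, define period by that date, and align the two sections that describe the timing.

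The cost is a few lines of plan and code. It needs no new data, provided that each woman's recruiting site and enrolment date are recorded. If unblinding has already taken place, the adjusted estimate should be labelled supportive instead.
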